### Physical/clinical measurements

Participants will be screened for cardiovascular risk factors by anthropometric and blood pressure measurements. Anthropometric measurements will be done according to international standards [43]. Waist and hip circumferences will be measured using an anthropometric tape and the waist to hip ratio (WHR) will be calculated. Height will be measured using a wall-mounted Harpenden stadiometer to the nearest 0.1 cm while weight will be measured using a wireless weight scale (Tanita body composition scale). The Tanita device will be used to calculate the body mass index (BMI) using the formula weight/(height (m) × height (m)). Office blood pressure including the brachial systolic and diastolic blood pressure and heart rate will be measured as described by Muntner and colleagues [44] in triplicates at three-minutes intervals after 10 min of rest in the seated position with an Omron M HEM-907XL Professional Blood Pressure Monitor (Omron Healthcare, Kyoto, Japan). This will be followed by 24 h ambulatory blood pressure measurement for determination of day time/night time blood pressure and dipping phenotype (A&D Instruments, Japan). Placental morphometry, architecture and vascularization which includes the uterine arteries, umbilical artery and middle cerebral artery, and uterine artery mean pulsality index will be determined by ultrasound.

### Clinical and laboratory investigations

Blood and early morning mid-stream urine samples will be obtained by the research nurse from each participant. Collected blood samples will be used for determining glucose, glycated haemoglobin (HbA1c), lipids (total cholesterol, LDL-cholesterol, HDL-cholesterol and triglycerides), creatinine and glomerular filtration rate (GFR), HIV viral load, CD4 count, insulin, oxidative stress markers [lipid peroxidation, total antioxidant capacity and 8-hydoxyl-2-deoxyguanine (8-OHdG)], endothelial function markers [endocan, assymetric dimethyl arginine (ADMA) and nitric oxide (NO)] and epigenetic markers (urine 5-methyl-2-deoxycytidine and trimethyl histone H3K9). Urinary albumin and creatinine concentrations will be determined in urine samples using approved standard analytical protocols. The homeostatic model assessment of insulin resistance (HOMA-IR) formula will be used to calculate insulin resistance from fasting glucose and insulin.

### Assessment of vascular functions

#### Pulse wave velocity (PWV)

PWV will be measured using the Vicorder device (SMT medical GmbH & Co. KG, Germany) as reported by Cauwenberghs and colleagues [45]. Prior to measurements, participants will lie in a supine position for 10 min after which a standard 10 cm pressure cuff will be placed on the upper right arm and blood pressure measurement taken. Thereafter, the standard 10 cm pressure cuff will be placed on the upper right thigh as high as possible towards the crotch. The centre between the base of the neck and chin will be palpated to identify the right common carotid artery pulse after which a neck band with an attached neck pressure cuff will be placed around the neck, positioning the cuff bladder exactly over the carotid artery pulse. These cuffs will be secured tightly enough to ensure a good coupling of both cuffs to the femoral and carotid arteries without discomfort to the participant. The distance between the two cuffs will be measured using a measuring tape and entered against the participants information on the Vicorder software which include height, weight and blood pressure (SBP and DBP). The vicorder device will be turned on to inflat both cuffs to about 60 mm Hg and waveforms will be recorded simultaneously over about 10 consecutive heartbeats to estimate transit time. The pulse wave velocity (m/s) will be calculated as the path length between carotid and femoral arteries/the transit time.

#### Retinal vessel analyses

Retinal vessel imaging will be captured with a non-mydriatic digital retinal camera (Optomed, Finland). A trained grader, masked to participant’s characteristics will perform the vessel measurements on the optic disc–centred image of both the right and left eye. After measurements, the retinal vessel dimensions, microvascular state and vascular tree will be analysed with semi-automated IFLEXIS software (VITO, Belgium) [46] by calculating the vessels widths and pattern features including the tortuosity, fractal analysis and lacunarity. The average diameter of venules and arterioles of the eye will be summarised as central retinal venular equivalent (CRVE) and central arteriolar equivalent (CRAE) respectively [47]. An overview of the different retinal features that will be calculated as reported in a previous study [48].

### Data management and integrity

This study will make use of the REDCap (Research Electronic Data Capture) system to capture all data elements. REDCap is a free web-based, secured and user-friendly electronic database software to support data capture and storage for research studies. It can easily be customized to suit the collection, storage and tracking of information and data from specific research studies [49]. The REDCap system will be managed by a dedicated Data Manager that will ensure the correct handling of the database. This will entail creating unique participant’s identifier number linked to their data with no association to their personal details thereby keeping participant’s data confidential.

### Proposed analysis

Data analysis which includes sample size determination and statistical analysis will be done by the project’s statistician.

#### Sample size calculation

The number of participants required to show statistical significance is based on previously published studies in which vascular function was assessed in HIV patients [50]. An error probability (α) of 0.05, and power (1 − β) of 0.80 and an average effect size (d) of 0.5 were used to calculate the sample size (n = 64 persons). Assuming a 25% drop out rate, we will use N = (64 + (64*25)/100) = 80 mothers/group to ensure that we will have enough sample size/group to show statistical significance. Total number of participating mothers will therefore be 160 (80 cases and 80 controls) and their offspring-160.

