#### Statistical analysis

Data analyses will be carried out using IBM statistical package for social sciences (SPSS) Version 23.0 (IBM Corp.). Armonk, NY, USA) and STATA. Data will be checked for normality using Shapiro-Wilks test and log-transformed and/or corrected for outliers when necessary. Descriptive statistics are presented as mean ± standard deviation (SD). Mean differences between groups (HIV positive pregnant women and HIV negative pregnant women) will be done using independent sample t-test. Analysis of variances (ANOVA) will be used to compare continuous variables between three or more groups. Multivariate analysis using multiple analysis of variance (MANOVA) will be used to compare continues variables for two or more independent variables (ART, HIV etc.). Chi-square test will be used to associate cardiovascular risk factors at baseline and follow-up for both mother and child. Pearson correlation will be used to assess relationship between risk factors of CVD. Linear and binomial logistic regressions will be employed to assess the risk of CVDs due to HIV and ART. A confidence interval of 95% will be taken and α = 0.05 will be considered for level of significance.

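### The 25% drop-out allowance multiplies where it should divide: 80 mothers per group leave 60 completers, not the required 64, and power is 77.5% rather than 80%

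*Protocol article*

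**What the plan says.** The protocol article's section on sample size calculation gives three design inputs. The first is "An error probability (α) of 0.05"; the power and effect size follow, "of 0.80 and an average effect size (d) of 0.5 were used". The result is stated as "were used to calculate the sample size (n = 64 persons". The next sentence applies the attrition allowance, "Assuming a 25% drop out rate, we will use N = (64 + (64*25)/100) = 80 mothers/group", and gives as its reason that each group will then be large enough to show significance. The section closes with the overall target: "Total number of participating mothers will therefore be 160 (80 cases and 80 controls) and their offspring-160".

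The statistical analysis section names the test for the comparison of HIV positive and HIV negative women, which "will be done using independent sample t-test", and repeats that "α = 0.05 will be considered for level of significance". No other section changes the drop-out rate or the recruitment target.

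**The concern.** The 25% is taken of the number needed at the end (64) and added to it. A drop-out rate describes the fraction of enrolled women who are lost, so the number to recruit is the number needed divided by the fraction retained. Adding the percentage instead always gives too few.

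At stake is whether the plan delivers the 80% power it states under its own attrition assumption. The starting figure has almost no slack, since 64 per group gives only just over 80%, so any shortfall in completers takes power below the stated level. This is also the only sample-size justification in the article.

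**Working it through.** **Inputs.** From the sample size section: α = 0.05, power 0.80, d = 0.5 (standardised, so SD = 1), 64 before drop-out, 25% drop-out, 80 per group, 160 in total. From the statistical analysis section: independent-sample t-test. Two readings have to be settled first:

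- *Sidedness* is not stated. I take the test as two-sided, because only that reproduces 64; a one-sided test needs 50.15, so 51 per group.
- *64 persons* is taken as per group, because the next sentence inflates it to mothers per group. As a total (32 per group) it would give only about 50% power.

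**Step 1: reproduce the plan's 64.** For a two-sided two-sample t-test with d = 0.5, α = 0.05 and power 0.80, the noncentral t calculation gives n = 63.77, rounded up to 64 per group. The plan's figure reproduces.

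**Step 2: reproduce the plan's 80.** 64 + 64 × 25/100 = 64 × 1.25 = 80 per group, and 2 × 80 = 160. The printed arithmetic is correct as arithmetic; the formula is the wrong one.

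**Step 3: apply the plan's own drop-out to 80.** 80 × (1 − 0.25) = 60 per group, and 64 − 60 = 4 short per group.

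**Step 4: the allowance that matches 25%.** 64/(1 − 0.25) = 85.33, so 86 per group and 2 × 86 = 172 mothers. That is 6 more per group and 12 more overall.

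**Step 5: the drop-out that 80 per group does cover.** 1 − 64/80 = 0.20, that is, 20%.

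**Step 6: power for d = 0.5, two-sided α = 0.05.** The normal approximation is Φ(d√(n/2) − 1.96). For n = 60: 0.5 × √30 = 2.739, and Φ(2.739 − 1.960) = Φ(0.779) = 0.782. The t-test column uses the noncentral t distribution, which matches the test the plan names.

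| Mothers per group | Situation | Power, t-test | Power, normal approximation |
|---|---|---|---|
| 80 | no loss | 88.2% | 88.5% |
| 64 | 20% lost from 80 | 80.1% | 80.7% |
| 60 | 25% lost from 80 | 77.5% | 78.2% |

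**Step 7: detectable effect.** With 60 per group and 80% power, the t-test detects d = 0.516, against 0.50 as planned: 0.516/0.50 = 1.032, about 3% larger.

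**The case against.** The best case for leaving the figure alone is that nothing of substance turns on it. The loss against 64 completers is 80.1 − 77.5 = 2.6 points on the t-test, and against the nominal 80% it is only 1.8 points on the normal approximation. The effect size is a round planning value, and uncertainty about it matters more: at 64 per group, power is 71% if d is 0.45 and 87% if d is 0.55. The calculation is also not tied to a particular visit. Mothers are measured from 11–14 weeks onward, and before any attrition 80 per group gives 88% power.

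Most of this stands, and it fixes the size and reach of the point. The shortfall is small and arises only once more than 20% of mothers have been lost; first-trimester comparisons with nearly complete data are unaffected. What the objection does not remove is the contradiction in print: a 25% rate, a target said to be sufficient under it, and a formula that covers only 20%. This is a stated figure and not a detail left to a fuller document, so an unseen analysis plan does not cure it.

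A reader might go further and infer that the planned power also fails, and by more, for the children at 24 months. The article does not support that. It makes no power claim for offspring. The figure of 160 is a head-count that follows from 160 singleton pregnancies, and it is not described as the number evaluable at 24 months. The article gives no rate of pregnancy or neonatal loss, and because it does not define drop-out, such losses may already sit within the 25%.

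**Conclusion.** The point holds as a minor error of arithmetic. Under the plan's own 25% drop-out, 80 mothers per group leave 60, not 64. Power for d = 0.5 is 77.5% and not the stated 80%, and the effect detectable with 80% power is 0.516. Eighty per group supports 20% drop-out; 25% needs 86 per group.

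The conclusion assumes a two-sided t-test at 0.05, equal groups, 64 read as per group, and drop-out understood as a fraction of the women enrolled. If the test were one-sided, 60 per group would give about 86% power, but then 64 would not follow from the stated inputs, so that reading replaces one inconsistency with another.

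The point is limited to comparisons of mothers after losses above 20%. It is not a finding that the study is inadequately powered throughout.

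**What to change.** Restate the allowance in the sample size section, for example: *80 mothers per group retain 80% power with up to 20% drop-out; at the assumed 25% drop-out, 60 per group complete and power is 77.5% for d = 0.5 (two-sided t-test, α = 0.05).* This costs one sentence and no extra recruitment; the only downside is a slightly less favourable stated power.

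The alternative is to keep both the 25% rate and the 80% power and plan 86 per group, 172 mothers. That is the dearer option: 12 more mothers, and their children, through repeated imaging, laboratory work and follow-up to 24 months. For a loss of about 2.6 points, restating the figure is enough.

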#### Statistical analysis

Data analyses will be carried out using IBM statistical package for social sciences (SPSS) Version 23.0 (IBM Corp.). Armonk, NY, USA) and STATA. Data will be checked for normality using Shapiro-Wilks test and log-transformed and/or corrected for outliers when necessary. Descriptive statistics are presented as mean ± standard deviation (SD). Mean differences between groups (HIV positive pregnant women and HIV negative pregnant women) will be done using independent sample t-test. Analysis of variances (ANOVA) will be used to compare continuous variables between three or more groups. Multivariate analysis using multiple analysis of variance (MANOVA) will be used to compare continues variables for two or more independent variables (ART, HIV etc.). Chi-square test will be used to associate cardiovascular risk factors at baseline and follow-up for both mother and child. Pearson correlation will be used to assess relationship between risk factors of CVD. Linear and binomial logistic regressions will be employed to assess the risk of CVDs due to HIV and ART. A confidence interval of 95% will be taken and α = 0.05 will be considered for level of significance.

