**Methods:**

A longitudinal case–control study in HIV positive pregnant women on ART and HIV negative pregnant women will be conducted. All pregnant women will be assessed for cardio-metabolic risk factors and markers (lipids, anthropometric and glycaemic indies, oxidative stress), hemodynamic status (blood pressure parameters) and vascular function (arterial compliance, retinal microvasculature, uterine artery mean pulsatility index). Child health will be monitored in utero and postnatally via routine foetal health screening, placental integrity, anthropometry, blood pressure parameters, markers of oxidative stress and endothelial function in cord blood and cardiovascular epigenetic markers in urine.

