### Selection criteria

Pregnant women of African ancestry with singleton uncomplicated 11–14 week old pregnancies, who are either HIV positive for the case group or HIV negative for the control group will be recruited for the study. Pregnant women with type 2 diabetes, gestational diabetes, renal and CVDs or any critical health condition will be excluded from the study. Furthermore, data will not be collected from eligible pregnant women who have eaten, smoked or done physical exercise 6 h prior to data collection.

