### Study design and experimental plan

A prospective case–control design will be employed for this study. This will include HIV positive pregnant women on ART and HIV negative pregnant women who will serve as control. HIV positive pregnant women below 35 years of age with singleton pregnancy on ART attending antenatal clinic at  Mthatha Regional  Hospital and Nelson Mandela Academic Hospital, Mthatha will be recruited for the study and followed up during pregnancy for the presence of cardiovascular risk factors. In addition, foetal health and cardiometabolic health of the babies born to recruited women will be assessed after birth and up to 24 months after birth.

Recruited, pregnant women with known HIV positive status and who have been on ART for over 4 months will be counselled and screened for HIV to confirm their status. Thereafter, pregnant women will be assessed during antenatal visits in the first trimester (11–14 weeks), second trimester (24–26 weeks) and third trimester (35–37 weeks) for cardiometabolic risk factors including obesity, hypertension, albuminuria, insulin resistance, dyslipidaemia, oxidative stress and endothelial dysfunction. The viral load and CD4 count will be determined in the mothers at baseline and third trimester of pregnancy. A structured interviewer administered questionnaire will be used to collect data on their baseline characteristics including demographic, obstetric and family history of CVDs while anthropometric and blood pressure measurements will be performed. Placental morphometry will be assessed by ultrasound while vascular health will be assessed via pulse wave velocity (Vicorder, SMT GmbH, Germany) and endothelial function markers in blood. Microvasculature assessment will be done via retinal imaging using a retinal camera (Optomed, Finland) as previously reported [40]. Blood samples will be collected for the assessment of endothelial function markers [41], oxidative stress, lipid profile and insulin resistance markers [42] while urine will be collected for assessment of renal function. Mothers will have one post delivery follow-up for CVD risk assessment.

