## Discussion

This ARTMOMSBABES study intends to investigate whether HIV-infected pregnant women on ART have a higher risk for cardiometabolic conditions and whether their offspring are borne with an increased risk for similar conditions. We are not aware of any study in sub-Saharan Africa that has utilised a longitudinal study model to assess the in utero effect of HIV/ART on cardiometabolic risk factors including vascular endothelial changes in pregnant women living with HIV and a follow up of their offspring. Existing studies have shown that the use of ART is associated with cardiovascular risk in people living with HIV [51–53] but little is known about the effect of HIV-infection and ART use in pregnant women and how these may affect the offspring exposed to both the in utero. The repeated measurements in the first, second and third trimesters of pregnancy will help to monitor changes if any in the progression of cardiometabolic risk as a result of HIV-infection and ART use in pregnancy. That is, whether there exist placental vascular changes due to ART. More so, follow-up of offspring after birth will be able to establish whether in utero expose to ART has long-term effects on the cardiometabolic health of children born of HIV-infected mothers on ART.

Findings from this study will provide information that may be helpful to develop guidelines on the use of ART and management of cardiovascular health in HIV-infected pregnant women in local health care settings. It will provide information on the cardiometabolic health of children born to HIV-infected pregnant women on ART for improved management and development of prevention policies. It will also contribute to the current global knowledge on HIV and CVD in pregnant women and children. The findings of this study may also provide an explanation and understanding of the high prevalence and early occurrence of cardiovascular risk in children especially in the South African context, as current evidence has reported increased prevalence of obesity, hypertension and other CVD risk factors in children [54–57]. These findings may also contribute to the establishment of cardiovascular disease and vascular endothelial endpoints in pregnancy which may be specific to the South African and African context but may also be useful to predict future cardiovascular events in children.

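### HIV and ART are completely confounded in this two-group design, so separate effects, and the ART-specific conclusions in the Discussion, are not available

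*Protocol article*

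**What the plan says.** The groups are described consistently. The Abstract (Methods) says: "A longitudinal case–control study in HIV positive pregnant women on ART and HIV negative pregnant women will be conducted". The section Study design and experimental plan repeats it: "This will include HIV positive pregnant women on ART and HIV negative pregnant women who will serve as control". The same section adds, for the positive women: "pregnant women with known HIV positive status and who have been on ART for over 4 months will be counselled and screened for HIV". Selection criteria names HIV status only: "who are either HIV positive for the case group or HIV negative for the control group will be recruited for the study". Sample size calculation counts two groups and no more: "Total number of participating mothers will therefore be 160 (80 cases and 80 controls) and their offspring-160".

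Two sentences in Statistical analysis bear on the point. MANOVA "will be used to compare continues variables for two or more independent variables (ART, HIV etc".), which lists ART and HIV as distinct independent variables. For the regressions: "Linear and binomial logistic regressions will be employed to assess the risk of CVDs due to HIV and ART".

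The Discussion then makes statements about ART alone. It says that the repeated measurements in pregnancy will show whether ART causes vascular changes in the placenta, and that "follow-up of offspring after birth will be able to establish whether in utero expose to ART has long-term effects" on the children's cardiometabolic health. The limitations paragraph covers the single ethnic population, the 24-month follow-up and the use of Western cut-offs. It does not mention that HIV and ART cannot be told apart.

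**The concern.** An ART effect can be separated from an HIV effect only if some women have one exposure without the other. None are planned. The analysis section names the two as separate variables, and the Discussion draws conclusions about one of them, so the text promises something that the data cannot contain.

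The stake is attribution. A difference between the groups could come from the infection, the drugs, both, or two effects that partly cancel. If it is reported as an effect of ART, it may be carried into the guidance on ART in pregnancy that the article hopes to inform.

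**Working it through.** **Inputs.** 80 cases, all HIV positive and on ART; 80 controls, all HIV negative (Abstract, Study design and experimental plan, Sample size calculation). Assumption: controls take no ART. The article does not say so in words, but it describes no ART-exposed HIV negative group.

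**The plan's own figure.** For d = 0.5, two-sided α = 0.05 and power 0.80, a two-sample t-test needs 63.77, so 64 per group (63 by the normal approximation). One-sided versions give 50 to 51 and do not fit. The stated allowance gives 64 × 1.25 = 80. The study is thus sized for one contrast between two groups.

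**Cell counts.**

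| | ART yes | ART no |
|---|---|---|
| HIV positive | 80 | 0 |
| HIV negative | 0 | 80 |

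**Main-effects model, both coded yes/no.** E(Y) = β0 + βH·HIV + βA·ART.

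- Mean in cases: β0 + βH + βA. Mean in controls: β0. Difference: βH + βA.
- X'X has rows (160, 80, 80), (80, 80, 80), (80, 80, 80). The last two rows are identical, so the determinant is 0 and the rank is 2 of 3. The correlation of HIV and ART is 1.0.
- Adding an HIV × ART term gives rank 2 of 4.

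**What this means in SD units.** The pairs (βH, βA) = (0.5, 0), (0, 0.5) and (1.0, −0.5) all give the same group difference of 0.5. No data from these groups can choose among them, and more women in the same two cells would not help.

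**If ART is coded otherwise.** Regimen or duration varies among cases, and the matrix then has full rank, 3 of 3. But the ART coefficient now compares one regimen with another, or longer with shorter use, among treated women. With duration set to 0 in controls, the HIV coefficient is an extrapolation to zero duration, which no case has, because all exceed 4 months. Neither coding compares ART with no ART.

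**If some untreated HIV positive women entered.** Selection criteria does not name ART, so suppose k of the 80 cases were off ART. The other sections do not support this. The standard error of the ART effect, in SD units, is √(1/k + 1/(80 − k)):

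| k | SE of ART effect | Variance inflation factor |
|---|---|---|
| 1 | √(1 + 1/79) = 1.01 | 40.5 |
| 5 | √(1/5 + 1/75) = 0.46 | 8.5 |
| 10 | √(1/10 + 1/70) = 0.34 | 4.5 |

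Against the planned effect of 0.5 SD, even k = 10 would be of little use.

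**The case against.** Several points on the other side are sound and limit the finding.

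- **The main comparison is sound as a comparison.** The t-test contrasts HIV positive with HIV negative women, and the sample size is for a two-group difference. A reader might infer that the analysis as a whole fails. It does not: with a redundant term removed, a model still fits and estimates the joint contrast.
- **The coding of ART is not given.** The article never defines ART as yes/no, it plans ANOVA for more than two groups without naming any, and the design flow figure is not shown. The singular matrix is therefore conditional on yes/no coding. The limit on interpretation is not: regimen or duration leaves it in place.
- **The regression sentence can be read as joint exposure.** The article often writes HIV/ART as one term, including in its objectives. That sentence alone does not prove that two separate terms are planned. The MANOVA wording and the Discussion are what need correcting.
- **Software behaviour.** One might say that the package would silently drop one term and give its effect the other's name. Nothing in the article supports that, and a redundant term is normally flagged.
- **ART begun before conception.** Over 4 months on ART is more than 4 × 30.44/7 = 17.4 weeks, beyond the 14-week upper limit at entry, so the cases began ART before conception. A reader might count this as a second error. It is a choice of scope: the article nowhere promises to study ART started in pregnancy.
- **The link to guidelines is hedged** in the Discussion as something that may help.

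What remains is unanswered: ART against no ART cannot be separated from HIV status, the Discussion says that it will be, and the limitations do not mention it.

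**Conclusion.** The point holds in this form. Under the two-group design, HIV and ART effects are not separately identifiable at any sample size. The MANOVA with ART and HIV as distinct variables cannot give separate yes/no effects. The statements that the study will show placental changes caused by ART, and settle whether in utero ART has long-term effects, are not available from these data.

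This rests on every case being on ART, as the Abstract and the design section say, and on controls being unexposed. It does not depend on the effect size, the dropout rate or the choice of outcome. The two-group t-test, the sample size calculation and the aim in Aim and objectives, read as a joint exposure, are untouched by it.

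This is an error in what the text promises, not a failure of the study. It should be corrected before results are reported, because it decides what the group difference may be called.

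**What to change.** 1. **Statistical analysis.** Replace ART and HIV as separate variables with one exposure term, HIV with ART versus neither, in the MANOVA and in the linear and logistic regressions.
2. **Discussion.** Reword the placental and offspring statements, and any other ART-only conclusion, so that they concern combined HIV/ART exposure.
3. **Limitations paragraph.** State that HIV and ART are completely confounded, and that a group difference cannot be attributed to either alone.
4. **Optional.** Add an exploratory analysis among cases only, by viral load and CD4 count, both already measured at baseline and in the third trimester. Include ART duration only if it is recorded: neither Data collection nor Clinical and laboratory investigations lists it, and the questionnaire file is not shown. Label it unpowered. An even split of 40 versus 40 has about 60% power at d = 0.5, and 32 versus 32 about 50%. It describes variation among treated women and does not restore the ART-versus-no-ART claim.

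Items 1 to 3 cost only rewording, with no change to recruitment, measurements or sample size. The price is a narrower claim.
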